### Trial interventions

All included patients will fast for 6–8 h before surgery and will be allocated to one of the following two study groups:
Low pneumoperitoneum pressure (LPP) group: 10 mmHg PP will be set during surgery.Standard pneumoperitoneum pressure (SPP) group: 15 mmHg PP will be set during surgery.

After anesthesia induction, the TEE probe will be gently inserted into the esophagus to assess the incidence and grades of gas embolism until the end of the surgery. Infusion will be performed through the peripheral venous line rather than the central venous catheter in order to reduce interference with the evaluation of gas embolism. The PP will be set at 10 or 15 mmHg throughout the operation, according to the group allocation. The patients will receive deep neuromuscular blockade with cisatracurium throughout surgery to maintain a train of four (TOF) = 0 and post-tetanic count (PTC) ≥ 1 to satisfy the operation space. To avoid the confounding factor of surgical skills, all surgeries will be performed by a surgeon for two groups and all patients. Neuromuscular blockade pharmacological reversion will be achieved with neostigmine (2.5 mg or 30–50 μg/kg), according to usual care.

### Standard procedures

To avoid interference with the trial intervention, routine elements of perioperative anesthesia care (including general anesthesia, postoperative pain management, physiotherapeutic procedures, and fluid management) will be performed according to the clinical routine of Zhongshan Hospital Fudan University. The following approaches are suggested (not mandatory) for anesthetic management:
Low CVP anesthesia will be administered during the operation. The CVP will be encouraged to be maintained at 5 ± 2 mmHg. Dobutamine (1–3 μg/kg/min) and nitroglycerin (5 μg/min) can be used to achieve a low CVP if necessary.Restrictive fluid therapy will be used to reduce the increase of intraoperative CVP until the liver mass is removed.Patients in both groups will be ventilated in a volume-controlled ventilation mode. The tidal volume (VT) will be set at 8 mL/kg predicted body weight (PBW), without intraoperative high positive end-expiratory pressure (PEEP). The respiratory rate will be set at 10–12 bpm, and the inspiratory to expiratory time (I:E) ratio will be 1:2.Preoperative invasive arterial blood pressure monitoring will be established for circulation management and perioperative blood gas analysis. The mean arterial pressure will be maintained at ≥ 60 mmHg.Cerebral oxygen and cardiac output are monitored during the perioperative period.Blood products will be given to maintain hemoglobin at a level > 8 g/dl (in patients with no history of ischemic heart disease or ≥ 10 g/dl otherwise).Normothermia and normoglycemia will be maintained throughout the surgical period.Appropriate prophylactic antibiotics will be used as recommended.Oxygenation (pulse oximetry) will be maintained at ≥ 94%. If hypoxemia, defined as peripheral oxygen saturation (SpO_2_) < 90% occurs for > 1 min, FiO_2_ will be increased in steps of 0.1 until 1.0, and recruitment maneuvers (RM) will be applied. If hypercapnia (P_ET_CO_2_ > 60 mmHg) with respiratory acidosis (pHa < 7.20) occurs, the respiratory rate will be increased (maximum 30/min), and VT will be increased stepwise up to 10 mL/kg PBW.

Other procedures will follow the Safe Surgery Checklist of the World Health Organization as published (www.who.int/patientsafety/safesurgery/en/index.html).

### Outcomes

The primary outcome will be the incidence of gas embolism ≥ grade 3 in the right atrioventricular system from the four-chamber cardiac plane of the middle esophagus; this will be detected by TEE (GE VENUE R2) over the duration of the LLR. The grades of gas embolism will be determined according to the Schmandra microbubble method as follows:

Grade 0: No bubbles observed in the right ventricular system

Grade 1: A single bubble observed in right atrium (RA), right ventricle (RV), or right ventricular outflow tract (RVOT).

Grade 2: Multiple bubbles observed, but only occupying  part of the RA, RV, or RVOT.

Grade 3: Multiple bubbles observed, occupying most of the RA, RV, or RVOT.

Grade 4: Bubbles occupying the whole RA, RV, or RVOT.

The secondary outcome measures will be as follows:
PQRSCorrelations between intraoperative IVC-CI and CVP. IVC-CI will be defined as (IVC_max_ − IVC_min_)/IVC_max_, which is the difference between the maximum inspiratory diameter and minimum expiratory diameter divided by the maximum inspiratory diameter in intubated patients with mechanical ventilation during LLR.Intra-operative complications (hypotension, hypothermia, hypoxia) related to gas embolismPostoperative organ dysfunction (Appendix 1)Postoperative complications within 30 daysNeed for unexpected intensive care unit (ICU) admission or readmissionNumber of hospital-free days at day 2890-day survivalIn-hospital survivalSatisfaction of surgeon

Blood samples will be collected preoperatively, in postanesthesia care unit (PACU), and on postoperative day (POD) 1. Samples will be analyzed centrally for CRP, hs-CRP, cTnT, NT-proBNP, and IL-1, IL-6, IL-8, and IL-10. The standard operating procedure for collecting and processing blood samples is available in Additional file 2.

### Quality of recovery

The Chinese version of the PQRS status test will be used to assess the quality of recovery in patients undergoing LLR (Additional file 3). The PQRS is a validated multidimensional patient report outcome tool [18, 21, 22] designed to assess patients’ recovery to baseline status in the postoperative period (www.postopqrs.com). In every patient, a baseline measurement of PQRS will be performed prior to surgery. After surgery, the measurement of the PQRS will be repeated 40 min after arrival in the post-anesthesia care unit (PACU), as well as in the ward on the morning of POD 1 and POD 3. The PQRS is a verbal survey tool that depicts recovery in the following five domains: physiologic, nociceptive, emotive, functional, and cognitive, and also collects the overall patient perspective. Each of these domains is assessed with multiple items on an ordinal scale and is compared to the baseline to evaluate recovery. Recovery is a dichotomized outcome defined by a return to baseline values or better at each postoperative measurement timepoint. Overall recovery requires recovery in all assessed domains, and failure in any of the domains results in failure of overall recovery.

### Study visits and data collection

Patients will be visited preoperatively, intraoperatively, daily between POD 1 and 3, and on discharge. Patients will be contacted by phone on PODs 30 and 90 (Fig. 2).

**Fig. 2 Fig2:**
[figure not shown]
Schedule of enrolment, interventions, and assessments. Pre-op, pre-operative; PACU, post-anesthesia care unit; POD, postoperative day; CVP, central venous pressure; IVC-CI, inferior vena cava-collapsibility index; PQRS, Post-Operative Quality of Recovery Scale

The patients will be screened according to the inclusion criteria. All patients meeting the inclusion criteria will be registered in a screening log file. The investigators will explain the course and purpose of the study and provide written information on the study. Patients willing to participate in the study will be required to provide written informed consent (Additional file 2).

Data will be registered in both the paper case report form (CRF) and the electronic case report form (eCRF) on electronic data capture (EDC) system by trial or clinical personnel under the supervision of the trial investigators. In the case of inconsistency, the paper CRF will be used as a gold standard.

The following data will be collected:

Pre-randomization and baseline characteristics: Demographic data, including age, height, weight, sex, and BMI; surgical characteristics, including preoperative diagnosis, and type, location, number, and size of the primary liver tumor; co-morbidities, including coronary heart disease Y/N and Canadian Cardiovascular Society (CCS) score if Y, chronic heart failure Y/N and New York Heart Disease Association (NYHA) score if Y, atrial flutter or fibrillation Y/N, premature systole Y/N, conduction block Y/N, pulmonary ventilation dysfunction Y/N, chronic obstructive pulmonary disease Y/N and specific therapy if Y, hypertension Y/N, diabetes mellitus Y/N, chronic alcoholism Y/N, obstructive sleep apnea-hypopnea syndrome Y/N, and active smoking Y/N; American Society of Anesthesiologists (ASA) physical status; preoperative use of statins Y/N; preoperative use of aspirin Y/N; biological indices, including CRP, hs-CRP, c-TnT, NT-proBNP, IL-1, IL-6, IL-8, and IL-10; values of blood routine examination, hepatic and renal function, and coagulation function; measurements at baseline in the operation room (without oxygenation) before anesthesia induction, including measurements of heart rate, respiratory rate, CVP, SpO_2_, non-invasive blood pressure (NIBP), invasive blood pressure (IBP), artery blood gas (ABG) analysis and cerebral oxygen saturation (PQRS-0 is measured pre-operatively as the baseline).

At randomization (stratification): risk of intraoperative exposure of hepatic vein Y/N, liver cirrhosis status Y/N, and history of abdominal surgery Y/N.

During the surgical procedure, the TEE probe will be placed through the esophagus until extubation, and the following data will be collected:
Anesthetic data: type and doses of hypnotics, opioids, and muscle relaxants; duration of anesthesia; total volume of maintenance fluid; total number of blood products; ventilator settings (VT, respiratory rate, PEEP, FiO_2_); baseline (and then hourly) values for P_ET_CO_2_; cerebral oxygen monitoring values; blood pressure (systolic, diastolic, and mean); cardiac index, stroke volume variation, and cardiac performance index measured by the PULSION medical system (not mandatory); infusion rate of vasoactive drugs (dobutamine, ephedrine hydrochloride, noradrenaline, and other), and hourly urine output.Surgical data: type of surgery, duration of surgery, total volume of blood loss, surgical complications Y/N, and surgeon satisfaction.Intraoperative TEE monitoring data: intraoperative gas embolism grade, baseline for IVC-CI, and eccentricity index (EI) after anesthesia induction, and the grades and duration during gas embolism occurrence. EI is used to evaluate right ventricular volume and pressure overload [23]. IVC-CI and EI will also be recorded at the time of trocar insertion, the beginning of hepatic parenchymal transection, hepatic tumor removal, and following completion of the surgery. Vital signs, CVP, P_ET_CO_2_, cerebral oxygen monitoring values, ABG, and IVC-CI will also be recorded when any grade of gas embolism is detected by TEE.

After the surgical procedure, the following indices will be collected before hospital discharge:
Postoperative care pathway (surgical ward Y/N and ICU Y/N)Daily lowest values for heart rate, blood pressure, peripheral O_2_ saturation, respiratory rate, and temperaturePlasma ALT, bilirubin, creatinine, lactate, CRP, IL-1, IL-6, IL-8, IL-10, NT-proBNP, and cTnT (standard laboratory values, if any)PQRS-1 (PACU), PQRS-2 (POD 1) and PQRS-3 (POD 3)Postoperative complications (Y/N, type, and date of diagnosis), including intra-abdominal hemorrhage, ascites, bile leakage, intra-abdominal abscess, and post-resection liver failurePostoperative pulmonary complications (Appendix 1), as assessed by finger pulse oxygen saturation, blood gas analysis (if any), and chest X-ray (if any)Unexpected ICU admission Y/NLength of stay in the ICU and surgical wardDate of hospital dischargeDeath (Y/N and date)

Thirty days after surgery:
Postoperative complications (Y/N, type, and date of diagnosis)Survival status (If the patient is deceased, date of death)

Ninety days after surgery:
Survival status (if the patient is deceased, date of death)

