#### Secondary outcomes

Postoperative organ dysfunction and complications within 30 days will be classified according to the classification described by Dindo et al. [24] and defined as a dichotomous composite endpoint, while ICU admission and readmission will be given as a percentage. Scores for PQRS will be given as the mean and standard deviation per time point per treatment arm. The correlation between IVC-CI and CVP will be tested using the correlation analyses.

The effect of the intervention on secondary binary outcomes will be assessed using the risk ratio and 95% CI calculated with Wald’s likelihood ratio approximation test and *χ*^2^ tests for hypothesis testing. The effects of the intervention on hospital-free days at day 28 will be estimated with a Student’s *t* test and reported as the mean difference between the two groups. The consistency of the findings of the Student’s *t* test for the hospital-free days at day 28 will be confirmed according to the mean ratio, as calculated by a generalized additive model considering a zero-inflated beta distribution.

Finally, 90-day mortality will be assessed using Kaplan–Meier curves, and hazard ratios with 95% confidence intervals will be calculated using Cox proportional hazard models without adjustment for covariates. The proportional hazard assumptions will be tested using scaled Schoenfeld residuals, and alternative parametric survival models will be used if the proportionality assumption is not sustained.

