## Discussion

This study is the first prospective randomized clinical trial to determine the effect of low PP versus standard PP on gas embolism using TEE during elective LLR. The findings from this study will provide scientific and clinical evidence of the role of PP.

Pneumoperitoneum is closely related to the formation of an air embolism intraoperatively. The overall incidence of intraoperative venous gas embolization was 38% in a study of robot-assisted laparoscopic radical prostatectomy [25] and CO_2_ embolization was observed in 69% of patients who underwent laparoscopic cholecystectomy [26].

LLR was first described in 1995, but developed more slowly than other laparoscopic procedures due to gas embolism and uncontrolled bleeding [27, 28]. An intra-abdominal pressure of 12–15 mmHg of CO_2_ is higher than the normal portal blood pressure of 6–10 mmHg and is therefore capable of reducing portal blood flow and alterations in hepatic function. Although the PP range of about 15 mmHg is routinely used, LLR may be correlated to a higher incidence of air accumulation with surgery of the portal system [29]. It has been reported that gas embolism occurred in 5/7 (71%) of animals that underwent whole laparoscopic hepatectomy, 3/7 (42%) of which experienced a series of arrhythmias correlated with gas embolism [30]. Moreover, venous CO_2_ embolization was detected in all 50 patients who underwent laparoscopic hepatectomy [31].

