Complications related to gas embolism should be considered carefully, as gas embolism resulting from pneumoperitoneum establishment has been shown to be associated with a 28% mortality rate after laparoscopic cholecystectomy [32]. CO_2_ gas embolism in laparoscopic surgery may also cause postoperative cardiac arrest [2], cerebral infarction [3], and even death [33]. We reported a case of CO_2_ embolism during laparoscopic nephrectomy without evidence of right-to-left shunt, in which the patient suffered from slurred speech and developed epileptiform seizures 9 h after the surgery [34]. Once gas embolism occurs during LLR, it may affect cardiopulmonary function and even cause neurologic deficits, resulting in delayed postoperative recovery. In this study, TEE will be used for gas embolism monitoring because it is capable of detecting 0.02 mL/kg of gas. Cerebral oxygen will also be observed to prevent cerebral embolism caused by micro emboli. TEE has no effect on cerebral oxygen because the baseline values are mainly related to cardiac function [35].

The occurrence of CO_2_ embolism likely depends on several variables. Surgical duration and size of parenchymal transection are likely to be directly proportional to the risk of gas embolism [36]. Intraperitoneal pressure may also play a role. Indeed, a higher PP led to higher degrees of embolization after laparoscopic IVC injuries in anesthetized pigs [13]. Hence, low-PP surgery is attractive, especially in reducing the incidence of embolism and its related complications. In addition, clinically, the most important benefit of low-PP is lower postoperative pain scores, which accelerate postoperative recovery [12]. No previous studies have compared the incidence of gas thrombosis in low versus standard PP during elective LLR. Therefore, we hypothesized that a low PP (10 mmHg) with controlled-low-CVP will lead to less severe gas embolism and promote postoperative recovery as compared to standard PP (15 mmHg) in elective LLR. To better evaluate the prognosis, PQRS will be used to assess recovery after LLR according to six dimensions of health, including physiologic, nociceptive, emotive, activities of daily living, cognitive, and overall patient perspective [18].

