This study also aims to determine the correlation between IVC-CI and CVP on postoperative outcomes. By restrictive fluid therapy, low CVP is achieved in LLR with the benefit of a clear surgical field and reduced blood loss [37]. Low airway pressure (AWP) also reduces bleeding from the hepatic vein [38]. Moreover, it is thought that the risk of pulmonary gas embolism decreases with low AWP when PP is lower than CVP [38]. For the purpose of low AWP, the ventilation tidal volume is set at 8 mL/kg without high PEEP. The relationship between low CVP and gas embolism remains controversial at present [13, 39]; however, there is a theoretic increased risk of CO_2_ embolism at insufflation pressures exceeding the CVP due to the presence of a pressure gradient in the venous circulation [8]. Positive PP can further accentuate this gradient by altering the intrahepatic hemodynamics, which are not reflected in the CVP [39]. Therefore, we compared the effects of IVC-CI and CVP based on different PPs.

In summary, this study will assess the feasibility and effects of low PP (10 mmHg) during LLR. Given the unavoidable air accumulation in laparoscopic surgery, along with a deficiency in scientific and clinical evidence of the efficacy of low PP, this study will provide useful information on this intraoperative management strategy.

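### Blood loss, transfusion, operating time, surgical complications and conversion are not pre-specified outcomes, and converted patients leave the study despite the all-randomised analysis rule

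*Protocol article*

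**What the plan says.** **Outcomes.** The primary outcome is an echocardiographic grade: "The primary outcome will be the incidence of gas embolism ≥ grade 3 in the right atrioventricular system". The secondary list covers recovery, the IVC-CI/CVP correlation, organ dysfunction, 30-day complications, unplanned ICU care, hospital-free days, survival and surgeon satisfaction. Its one intra-operative complication item is restricted to low blood pressure, low temperature or hypoxia attributed to gas embolism.

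**Data collected.** Study visits and data collection lists, under surgical data, "type of surgery, duration of surgery, total volume of blood loss, surgical complications Y/N, and surgeon satisfaction". Under anesthetic data it lists "total number of blood products". Conversion to open surgery is not among the listed items.

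**Analysis.** Under Secondary outcomes, organ dysfunction and 30-day complications are "defined as a dichotomous composite endpoint", and binary outcomes are compared by risk ratio and chi-square test. No analysis section ties blood loss, blood products, operating time or surgical complications to a comparison of the arms.

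**Conversion.** Study dropouts says that converted patients are excluded from the study, with their data used up to that moment. The Analysis section says that all outcomes are analysed in all randomly assigned cases.

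**Purpose.** The Discussion ends by saying that "this study will assess the feasibility and effects of low PP (10 mmHg) during LLR".

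**The concern.** The intervention is a fixed pressure: "The PP will be set at 10 or 15 mmHg throughout the operation, according to the group allocation". Trial interventions justifies deep neuromuscular block by the need for operating space, so the authors recognise exposure as a constraint. The Discussion says that LLR "developed more slowly than other laparoscopic procedures due to gas embolism and uncontrolled bleeding". The first of those two hazards is the primary outcome. Intra-operative bleeding, the more direct form of the second, is measured but is not an outcome.

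Two things are at stake. First, if low pressure reduces embolism, readers will ask what it cost in the operating room, and the answer will rest on comparisons that were not pre-specified. Second, conversion is a direct sign that the operation could not be completed as planned. If converted patients leave at that moment, their later bleeding, transfusion and complications may not be counted in the arm to which they were randomised.

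**Working it through.** **Step 1: set the items against the text.**

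| Item | Data item? | Outcome? | Comparison of arms stated? |
|---|---|---|---|
| Total blood loss | Yes | No | No |
| Blood products | Yes | No | No |
| Duration of surgery | Yes | No | No |
| Surgical complications Y/N | Yes | No | No |
| Conversion to open surgery | Not listed; discontinuation reasons go in the CRF | No | No |
| Surgeon satisfaction | Yes | Yes | Not by name |
| 30-day complications | Yes, including intra-abdominal bleeding and bile leak | Yes, within a composite | Yes |

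The gap is in direct intra-operative measures. Later harm is covered in part.

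**Step 2: set the two rules on converted patients side by side.** The Analysis section keeps every randomised patient for every outcome. Study dropouts ends a converted patient's data at conversion. Both cannot hold for outcomes that arise afterwards: 30-day complications, ICU admission, hospital-free days and 90-day survival. The cut-off also truncates total blood loss and operating time, and does so in cases that may be among the most difficult. If conversions were more frequent in one arm, and converted patients did worse, the truncation would flatter that arm. The documents give no conversion rate, so this bias has a direction but no size.

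**Step 3: does the remedy change the sample size?** Reproduce the plan's figure first, with p = 0.45 and 0.69, two-sided 5% and 80% power:

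n per arm = (0.45×0.55 + 0.69×0.31) × (1.960 + 0.842)² / 0.24² = 62.87, so 63 per arm and 126 in total. Then 126 / 0.90 = 140.

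The stated 126 and 140 are reproduced. Safety outcomes reported as estimates do not enter this calculation.

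**Step 4: what precision would the trial give?** For a continuous measure (suitably transformed if skewed), the 95% half-width in SD units is 1.96 × √(2/n):

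- n = 70 per arm: 1.96 × 0.169 = 0.33 SD
- n = 63 per arm: 1.96 × 0.178 = 0.35 SD

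The difference detectable with 80% power is 2.802 × √(2/n), which is 0.47 SD at 70 per arm and 0.50 SD at 63.

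For binary harms the documents give no rates, so the pairs below are assumptions (normal approximation, two-sided 5%):

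| Assumed rates | Power, 63 per arm | Power, 70 per arm |
|---|---|---|
| 2% vs 5% | 15% | 16% |
| 5% vs 10% | 18% | 20% |
| 5% vs 15% | 46% | 51% |
| 10% vs 20% | 35% | 38% |
| 10% vs 30% | 81% | 85% |

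Of these pairs, only the 20-point difference reaches 80% power. Uncommon harms can be described but not tested.

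**The case against.** The strongest reply is that harm is already covered. Thirty-day complications (which include intra-abdominal bleeding and bile leak), organ dysfunction, unplanned ICU care and survival are secondary outcomes, and adverse events go to an independent monitoring committee. This stands. A reader might infer that the trial could favour low pressure without testing its cost at all, or that bleeding goes unexamined. The documents do not support either reading. What is missing is the direct intra-operative layer; the later layer is present, though partly in a composite.

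A reader might also infer that conversions will not be reported. That cannot be established: the flow diagram is not shown, discontinuation reasons are recorded, and descriptive tables may sit in an analysis plan that is not at hand. The point is limited to the stated outcome list and the stated exclusion.

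No section says that low pressure causes bleeding, and the Discussion links blood loss to venous and airway pressure. That is correct. The case for these outcomes is that the trial should look, not that harm is expected.

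The Discussion says "Surgical duration and size of parenchymal transection are likely to be directly proportional to the risk of gas embolism". A reader might infer that longer surgery under low pressure would distort the primary result. This does not follow. Embolism is assessed over the whole resection, so events in any extra time already count against the arm in which they occur, and a proportional change in exposure does not translate directly into a binary incidence.

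Finally, the Objectives section makes no feasibility claim; that wording comes from the Discussion's summary. This weakens the argument from purpose but leaves the conflict over converted patients untouched.

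**Conclusion.** The point holds in a limited form. Five direct intra-operative measures are absent from the outcome list, although four of them are already collected. Separately, the rule that converted patients leave the study contradicts the rule that all randomised patients are analysed, and it can drop the harms of patients in whom the assigned pressure failed.

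The first part is a design choice that is cheap to improve. The second is a contradiction that must be reconciled. Neither changes the primary hypothesis test or the sample size. Precision for continuous measures is about ±0.33 to ±0.35 SD, on the assumption of 70 to 63 analysed patients per arm. Power for uncommon binary harms is about 15% to 51% over the assumed pairs from 2% vs 5% to 5% vs 15%, so a non-significant difference in them would not show safety.

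**What to change.** 1. In Outcomes, add as secondary (safety) outcomes: total blood loss, any transfusion, duration of surgery, surgical complications, and conversion to open surgery with its reason.
2. Report each by arm in all randomised patients, as a difference or ratio with a 95% confidence interval and without significance claims.
3. Reconcile Study dropouts with the Analysis section, so that converted patients stay in follow-up and in the analysis of the arm to which they were randomised. Their blood loss, transfusion and operating time should cover the whole operation.
4. Add conversion and its reason as data items.

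The cost is small. N stays at 140, and four of the five measures are already collected. Conversion needs a field of its own, and follow-up after conversion must be kept up. The downside is a longer list of secondary comparisons, which reporting as estimates keeps in proportion. Because enrolment has started, the change should be made as a documented amendment, with the registry updated, before any comparison by arm.
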